### Calculations and analyses

Considering previous studies on the complications of pain treatments [14, 46], we expect that their rapid detection using alarms might yield moderate between-group differences in primary measures, that is, pain intensity and frequency and duration of side effects (Cohen’s *d* = 0.5). Despite being only speculative, it is also possible that patients allocated to the app without alarm will perform better than those allocated to TAU, if they also perceive that they are being telemonitored even though they are not. However, we expect this effect to be small. Considering 80% power, we will need 50 participants in each group to perform the analyses. Power calculations were made with G*Power [47]. Data will be analyzed using the intention-to-treat principle and a mixed-model approach [48]. Changes in secondary measures will also be explored, although they are expected to be small because they are not the main target of medical intervention in the present study. Analyses will be performed separately by the lead researcher, [name], and an independent researcher. Interim analyses will not be performed because no harm is expected from adding the app to the usual treatment. The final dataset and the statistical code will be publically accessible to all researchers under request, excluding any personal information from the participants. Changes to eligibility and other protocol modifications, if any, will be discussed and communicated to relevant parties (Ethical Review Board, clinicians, participants, and journals).

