**Methods:**

The study will be a randomized controlled trial with three groups: treatment as usual (TAU), TAU+app, and TAU+app+alarms. All groups will receive the adequate treatment for their pain, which will be prescribed the first day of study according to clinical guidelines. Assessment in the TAU group will be the usual at the Pain Clinic, that is, a paper-and-pencil evaluation at the onset of treatment (beginning of study) and at follow up (end of study, 30 days later). The other two groups (TAU+app and TAU+app+alarms) will be assessed daily using Pain Monitor, a smartphone app developed by our multidisciplinary team. Telemonitoring will only be made in the TAU+app+alarms group. For this group, physicians at the Pain Clinic may decide to adjust pain treatment in response to alarms. Telemonitoring is not the usual practice at the Pain Clinic and will not occur in the other two groups (TAU and TAU+app), so no changes in treatment are expected in these groups after the first appointment. The total sample size will be 150, with 50 patients in each group. The assessment protocol will be the same in all groups and will include pain intensity and side effects of the medication (primary outcomes), together with several pain-related variables like pain interference, activity level, use of rescue medication, pain catastrophizing, and pain acceptance, among others.

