### Trial status

The trial is currently recruiting. Recruitment started in September 2017 and will continue until 150 participants have been included.

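### The 80% power claimed for 50 per group at d = 0.5 rests on an undeclared one-sided test or correlation; unadjusted two-sided power at 5% is about 70%, with nothing added for loss

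*Protocol article*

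**What the plan says.** The sample size rationale is in the Protocol article under Calculations and analyses. Rapid detection through alarms "might yield moderate between-group differences in primary measures, that is, pain intensity and frequency and duration of side effects", and the size attached to this is Cohen's d = 0.5. The conclusion is: "Considering 80% power, we will need 50 participants in each group to perform the analyses". G*Power is named as the software. The same paragraph allows that the app without alarms might also do better than usual treatment, and adds: "However, we expect this effect to be small". The analysis is described as intention-to-treat with a mixed model.

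The Abstract (Methods) repeats the size: "The total sample size will be 150, with 50 patients in each group". Under Trial status, recruitment "will continue until 150 participants have been included".

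The article does not state alpha, whether the test is one- or two-sided, which pair of groups (or which three-group test) the 50 refers to, any correlation between repeated measurements, or a dropout rate. The Design section calls this a superiority trial, and the Pain monitor section expects lower pain and fewer side effects in the alarm group. Neither says that testing is one-sided.

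**The concern.** Effect size, power and group size are printed together as one claim, so they should agree under some stated test. A reader who meets d = 0.5, 80% power and no mention of sidedness will assume a two-sided 5% comparison of two groups. On that reading the three numbers do not agree, because 64 per group are needed.

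The second matter is loss. The article says 50 per group are needed for the analyses and then recruits exactly 3 × 50 = 150. Patients are followed for 30 days, with two app entries a day in two of the arms, so some missing outcome data should be expected.

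What is at stake is how a null result would be read. The trial would be taken to have had a one-in-five chance of missing the planned effect, when under ordinary two-sided unadjusted testing that chance is about three in ten before any loss.

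**Working it through.** **Inputs from the article:** d = 0.5, power 80%, 50 per group, three groups, 150 recruited.
**Assumed, because not stated:** alpha 0.05; loss of 10% to 20%.

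**1. Reproducing the stated 50.** Normal approximation, n per group = 2(z_α + z_β)² / d².
- One-sided 5%: 2 × (1.645 + 0.842)² / 0.25 = 49.5, so 50.
- Two-sided 5%: 2 × (1.960 + 0.842)² / 0.25 = 62.8, so 63.

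The noncentral t, which is the two-sample t-test calculation, gives 50.15 (51) one-sided and 63.77 (64) two-sided. The printed figure is therefore reproduced by a one-sided 5% test.

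**2. Power at 50 per group.** Noncentrality = d√(n/2) = 0.5 × √25 = 2.5, with 98 degrees of freedom.

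| Test | Critical t | Power |
|---|---|---|
| One-sided 5% | 1.661 | 79.9% |
| Two-sided 5% | 1.984 | 69.7% |

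Solving for the effect that gives 80% power two-sided at n = 50 yields d = 0.566.

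**3. Three-group F test at N = 150, alpha 5%.**
- f = 0.25: 78.0% power; 80% needs 159 in total.
- Means 0, 0, 0.5 SD, so f = 0.5√2/3 = 0.236: 72.7% power; 80% needs 177.

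Neither gives 150.

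**4. Two-sided routes that do reach about 80%, and what each needs.**
- *Baseline adjustment.* The effective size is 0.5/√(1 − r²). Setting it to 0.566 gives r = √(1 − (0.5/0.566)²) = 0.47.
- *Repeated-measures between-groups F*, with two groups, two measurements, ρ = 0.5 and f = 0.25. Noncentrality = 0.0625 × 100 × 2 / 1.5 = 8.33, power 81.6%; 98 in total suffice.
- *Alarm arm against the other two pooled.* Noncentrality = 0.5/√(1/50 + 1/100) = 2.89 with 147 degrees of freedom, power 81.8%.

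The article states none of these assumptions.

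**5. Loss.** Allowance built in: 150 − 3 × 50 = 0. Two-sided, unadjusted, d = 0.5:

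| Assumed loss | Analysed per group | Power |
|---|---|---|
| 0% | 50 | 69.7% |
| 10% | 45 | 65.0% |
| 20% | 40 | 59.8% |

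With 45 per group, 80% power needs an effective size of 0.597, so r = √(1 − (0.5/0.597)²) = 0.55.

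**The case against.** The best defence is that the two-sided unadjusted t-test is the reviewer's benchmark and not the article's. The trial is called a superiority trial, its hypothesis is directional, and one-sided 5% testing gives 50. The planned analysis is a mixed model and every arm is measured before treatment and at the end, so an unadjusted comparison at one time point may understate the power. Three two-sided routes reach about 80% (step 4 above). Details of the model may also belong in a fuller document.

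Much of this stands. It rules out two stronger readings that a reader might draw. The first is that 50 per group cannot be reproduced at all; it can. The second is that the risk of missing the planned effect is simply 30% and not 20%. That holds only for a two-sided, unadjusted, two-group comparison, and the article does not say that this is the analysis.

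What does not stand is that nothing needs correcting. A directional expectation is not a declared one-sided test. Pooling the two comparison arms would sit badly with the Background section, which uses the app-only arm separately to isolate telemonitoring from app use. The correlation routes depend on a value of about 0.5 that is nowhere given. The repeated-measures F also averages in the pre-treatment score, so it may not be the contrast of interest.

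A third tempting inference is that the alarm-versus-app comparison is far weaker still. If the app alone were worth d = 0.2 and 0.5 were measured against usual treatment, the remaining 0.3 would have 32% power, and the app alone against usual treatment 17%. The documents do not support these as findings: they give no size for the app-alone effect, call it speculative, and do not say which comparator the 0.5 refers to.

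**Conclusion.** The power statement is wrong as a reader would take it, and it cannot be verified as written. On a two-sided 5% unadjusted comparison, 50 per group gives about 70% power at d = 0.5, and the shortfall against 80% is 14 patients per group (64 − 50). The likeliest source of the figure is an undeclared one-sided test, but that is an inference. The lack of any allowance for loss follows directly from the article's own numbers. The 65–60% range rests on an assumed loss of 10–20%, alpha of 5% and no covariate adjustment. The defect lies in the stated justification and its missing inputs. It does not show that 150 patients are too few under every reasonable analysis.

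**What to change.** Keep 150 patients and make three changes under Calculations and analyses.

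1. Replace the power sentence with wording such as: *With a two-sided 5% test, 50 per group gives about 70% power for d = 0.5 unadjusted (80% for d = 0.57), and about 60–65% if 10–20% of patients are lost.* Name the comparison and the test behind the number, and say that recruitment includes no allowance for loss.
2. State that the mixed model for pain intensity adjusts for the pre-treatment score already collected. Add that 50 per group reaches 80% if the baseline to day-30 correlation is at least about 0.47, or 0.55 with 10% loss. This gain is shown for pain intensity only; for side effects the unadjusted figure should stand unless a similar case is made.
3. If one-sided testing is intended, declare it and its alpha.

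Any figure for alarm versus app that allows for a small app-alone effect should be labelled as an assumption, with the comparator for d = 0.5 named.

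The cost is a reworded paragraph and one model term, with no added patients. The stated power becomes less favourable unless the correlation supports it. Holding 80% on the unadjusted two-sided basis would instead need 3 × 64 = 192 patients before any allowance for loss.

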## Discussion

Treatment of pain can be complex due to individual differences in response to interventions, the vast repertoire of available treatments, side effects associated with certain interventions, and the challenges of choosing the right dosage for a given patient [42–44, 49]. Thus, personalized treatments are urgently required. EMA has been argued to be a prerequisite to achieve this improvement in the effectiveness of treatments for chronic pain [17, 50]. There are important problems associated with the use of paper diaries for assessment of EMA, including recall bias and limited naturalistic value [51, 52]. The use of an app is a promising way of dealing with limitations of paper diaries, and is an easy tool for use in telemonitoring.

In the present study protocol, we describe a RCT designed to test the utility of Pain Monitor, an app for daily assessment of adults with chronic pain. The study aims to explore whether the use of the app results in improved pain treatment by adding a telemonitoring tool, that is, alarms in the presence of undesired events like side effects of the medication, lack of response to treatment, or excessive use of rescue medication. To the best of our knowledge this is the first study to evaluate the impact of a smartphone app for telemonitoring in pain settings and should reveal whether daily monitoring indeed improves treatment effectiveness.

The present study has some limitations. Blinding participants and healthcare professionals to allocation was not feasible for ethical reasons. Also, the app is still not available for the iOS operating system, so a subset of patients will not be able to participate in the study. We expect this number to be small because, in Spain, 90% of smartphones use the Android operating system [53]. If, indeed, results suggest that the use of the app (with or without alarms) leads to improved treatment, Pain Monitor will be developed for the iPhone operating system.

Despite these limitations, if telemonitoring with Pain Monitor leads to the hypothesized results, this will have important clinical implications. Specifically, we expect that daily use of Pain Monitor with alarms will lead to more effective and safer treatments, thanks to the rapid detection of non-response to the intervention prescribed for pain and side effects of the medication. Additionally, the use of Pain Monitor might also be useful to detect changes in other pain-related variables, such as pain interference, activity level, or psychological constructs like pain catastrophizing or pain acceptance, which are key elements in the multidisciplinary treatment of chronic pain [54]. If the results support the use of Pain Monitor, the findings will be communicated to the relevant groups, including the Hospital Board Committee, healthcare professionals, and patients. Also, results will be disseminated to the wider public via scientific publication.

### Trial status

The trial is currently recruiting. Recruitment started in September 2017 and will continue until 150 participants have been included.

## Abbreviations

EMA: Ecological momentary assessment
RCT: Randomized controlled trial
SPIRIT: Standard Protocol Items: Recommendations for Interventional Trials
TAU: Treatment as usual
